## Recruitment

10

Participants will be recruited through social/traditional media, workplaces, word-of-mouth, bus advertising, professional networks, and co-promotion through other related projects. To minimise self-selection based on a preference for PA, promotional materials will be framed to focus on health generally, noting the potential for smartcard credit (i.e. ‘Does taking the bus = better health? Want to earn over 50 free bus trips?’). Recruitment materials will direct potential participants to a study website and provide email and telephone contact details. The study website will provide more detailed information, including a link to the screening survey.

The recruitment phase will occur in two waves, with Wave 1 commencing in September 2019 and Wave 2 commencing in February 2020. The reason for conducting recruitment in two stages is to reduce resource burden and to lessen the impact of seasonal variation in PA and public transport use. Each recruitment wave is expected to take up to three months but will be extended if necessary. The positive response (n = 1091) with minimal advertising in a two-week period in our 2017 transport and physical activity behaviour project indicates high feasibility of this approach [22]. Participants will be directed to register their interest via the study website page, email or telephone contact. To facilitate recruitment, all participants (irrespective of group allocation) will receive smartcard credit to a maximum value of $30 (AUD) as study compensation. Compensation will be commensurate with participation and is independent of the incentives scheme: completion of the baseline assessment (T1) = $5 credit; completion of the post-intervention assessment (T2) = $10 credit; and completion of the follow-up assessment (T3) = $15 credit. Greater compensation for greater participation will be employed as a strategy to enhance retention and mitigate drop-out, particularly among the control group. This small amount of compensation was considered unlikely to alter usual travel behaviour.

## Assignment of interventions

11

### Allocation

11.1

After completion of the baseline assessment (T1), participants will be randomly allocated to the control or intervention arm. The allocation sequence will be created using computer-generated random numbers on a 1:1 ratio without stratification. Randomisation will be conducted in blocks of four, the details of which will be unavailable to research team members who enrol participants in the respective study arms.

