## Eligibility criteria

6

Prospective participants’ eligibility will be determined via an online or telephone screening questionnaire (Fig. 2). Inclusion criteria include: ≥ 18 years old; sufficient English proficiency to provide informed consent; living in Southern Tasmania; able to access an urban Tasmania bus service (participant defined); making trips by motor vehicle that could be made by bus; current infrequent bus user (on average ≤ 2 trips per week in the past six months); possession or willingness to possess a public transport smartcard; willingness for the public transport provider and the researchers to access smartcard data; possession of a mobile phone. Exclusion criteria include: intending to move house or work location whereby an urban bus service in Southern Tasmania will be inaccessible within the 10-month study period; currently engaged in or planning to engage in other incentive-based programs to enhance public transport use; pregnancy; a health condition that prevents walking; a health condition that prevents bus use; and a planned activity that would prevent bus use for greater than two weeks during the four month intervention phase of the 10 month study period e.g. surgery, extended holiday.

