### Blinding

11.2

Due to the nature of the intervention, participants cannot be blinded to treatment allocation. All members of the research team will be blinded except for two research assistants (RAs). The unblinded RAs will be responsible for enrolling participants, assigning participants to the control or intervention arms according to the treatment allocation sequence generated through the software Research Electronic Data Capture (REDCap, Version 8.5.19, Nashville, Tennessee, USA), informing participants of the requirements of being in the respective study arm, advising participants in the intervention arm if they have met their weekly bus trip target and the subsequent weekly target, coordinating clinic assessments and overall be the main contact point for participants. The unblinded RAs will not be involved in conducting the post randomisation clinic assessments at T2 and T3 or data analysis. The research team member who creates the randomisation sequence will have no contact with participants and will not be involved with data collection or analysis. There are no foreseen circumstances by which unblinding of other research team members would need to occur.

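### A constant, published block size of four, with the same two unblinded assistants enrolling and assigning, makes up to a third of allocations predictable and weakens concealment

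*Protocol article*

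**What the plan says.** Section 11.1 (Allocation) describes a list made from "computer-generated random numbers on a 1:1 ratio without stratification". The block rule follows: "Randomisation will be conducted in blocks of four, the details of which will be unavailable to research team members who enrol participants". On timing it says: "After completion of the baseline assessment (T1), participants will be randomly allocated to the control or intervention arm".

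Section 11.2 (Blinding) sets out the roles. All staff are blinded apart from two research assistants, and of these it says: "The unblinded RAs will be responsible for enrolling participants, assigning participants to the control or intervention arms according to the treatment allocation sequence". They also tell participants what their arm involves, report weekly target results to the intervention arm, coordinate clinic assessments and act as the main contact. Two separations are stated. The first concerns the person who makes the list: "The research team member who creates the randomisation sequence will have no contact with participants". The second limits the assistants' later role: "The unblinded RAs will not be involved in conducting the post randomisation clinic assessments at T2 and T3 or data analysis". The baseline assessment (T1) is not named in that exclusion.

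**The concern.** Withholding the block details is meant to stop those who enrol from foreseeing the next arm. It protects little if the same people handle each allocation as it is made and the block is short and always the same length. The past allocations and the block size together reveal the end of every block. No stratification and only two assistants make the running order easy to follow.

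What is at stake is selection bias. Someone who knows the next arm could influence which participant is scheduled or completed next. The outcome is behavioural, participants know their arm, and willingness to change travel habits is not captured by baseline step count. The Sample size section targets 624 steps/day against a standard deviation of 3500, that is 624/3500 = 0.18 standard deviations, so the trial looks for a small effect.

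**Working it through.** The protocol gives no figure for predictability, so there is none to reproduce. The check is an exact enumeration.

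**Inputs.** Block size 4, ratio 1:1 and no strata (section 11.1). Planned number randomised 350 (Sample size). The same two people enrol and assign (section 11.2).

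**Assumptions about the observer.** The assistant knows or has inferred the block size, knows where a block starts, and follows both assistants' allocations in order. Inference is feasible. Under unrestricted 1:1 allocation a given run of four splits 2:2 with probability 6/16 = 0.375, so five such runs in a row would occur with probability 0.375^5 = 0.7%. With blocks of four it happens every time.

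**Certain allocations.** There are 6 equally likely arrangements of AABB. An allocation is certain once one arm's two places in the block are used.
- Positions 1 and 2: probability 0.
- Position 3: certain if the first two are alike (AA or BB), 2 of 6 arrangements = 1/3.
- Position 4: always certain, probability 1.

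The sum is 0 + 0 + 1/3 + 1 = 4/3 per block, and (4/3)/4 = 1/3 of allocations. For 350 participants there are 87 full blocks and two left over in positions 1 and 2: 87 × 4/3 + 0 = 116.

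**Best guess** (always guess the arm with more places left).
- Position 1: 1/2.
- Position 2: 2/3.
- Position 3: 1/3 × 1 + 2/3 × 1/2 = 2/3.
- Position 4: 1.

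The mean is (1/2 + 2/3 + 2/3 + 1)/4 = (17/6)/4 = 17/24 = 70.8%.

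**Alternatives.** Fixed sizes were enumerated in the same way. Mixed sizes, each equally likely, were simulated (300 lists of 350), with an observer who knows the set of sizes and the whole history but not the size of each block.

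| Block scheme | Certain in advance | Best guess correct |
|---|---|---|
| Fixed 4 (as planned) | 33.3% | 70.8% |
| Fixed 6 | 25.0% | 68.3% |
| Fixed 8 | 20.0% | 66.6% |
| Mixed 4, 6 | 5.3% | 69.4% |
| Mixed 4, 6, 8 | 2.3% | 68.2% |

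Varying the size removes nearly all certainty, because the end of a block can no longer be recognised. It does little to the best guess, because any blocking leaves the lagging arm more likely to come next. Setting 71% against the 50% of simple randomisation would therefore overstate what the change achieves.

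**Arm imbalance.** The largest final difference is half of the largest unfinished block: 4/2 = 2 now, 8/2 = 4 with sizes up to 8.

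**The case against.** A reader might infer that a third of allocations are known in advance and that the stated concealment is undone. The documents do not support that.
- Section 11.1 withholds block details from those who enrol. One third is an upper limit for an assistant who gets round this, and nothing shows that either assistant had read the published block size while randomising.
- The list is made by someone without participant contact, and nothing says the assistants can see future entries.
- Sections 11.1 and 11.2 do not contradict each other. Staff who are denied the block details may still learn each allocation as it happens.
- The room for steering is limited. Under Eligibility criteria, "eligibility will be determined via an online or telephone screening questionnaire", against listed criteria. Allocation comes only after T1, which includes a survey and seven days of accelerometer wear, and participants largely control when these are finished.
- Steps are measured by device, with a baseline before allocation, so an imbalance in steps would show. The assistants take no part in T2 and T3 clinic assessments or in analysis.
- A single running list is inferred from the absence of stratification. Recruitment has two waves, and separate lists are not ruled out.

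All of this stands and limits the strength of the point, but it does not remove it. The assistants coordinate clinics and are not excluded from T1, so some influence on the order of randomisation remains. An imbalance in motivation would not show in baseline steps. Separate lists per wave would leave the one-third figure essentially unchanged.

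**Conclusion.** The point holds as a weakness in concealment. One short, constant and published block size, with the same unblinded assistants enrolling and assigning, lets an assistant who knows or infers the size and tracks the order predict up to one third of allocations with certainty, about 116 of 350. The size of any resulting bias in steps/day is not estimated and cannot be from the documents. No misconduct is suggested. Because the remedy costs almost nothing and cuts certain allocations to about 2%, it is worth making as a cheap improvement.

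**What to change.** Generate the REDCap allocation list with randomly varying block sizes, for example 4, 6 and 8, and keep the sizes undisclosed until recruitment ends. Section 11.1 would then say only that block sizes vary at random and will be reported after recruitment. If Wave 1 has started, make the change from Wave 2. No change is needed to the order of T1 and allocation, which is already as it should be.

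The cost is a new allocation table and one revised sentence; sample size and analysis are unaffected. The final arm sizes may differ by up to 4 instead of 2. If Wave 1's last block is left unfinished when the list changes, up to 2 more could be added (2 + 4 = 6). Either is trivial among 350.

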### Blinding

11.2

Due to the nature of the intervention, participants cannot be blinded to treatment allocation. All members of the research team will be blinded except for two research assistants (RAs). The unblinded RAs will be responsible for enrolling participants, assigning participants to the control or intervention arms according to the treatment allocation sequence generated through the software Research Electronic Data Capture (REDCap, Version 8.5.19, Nashville, Tennessee, USA), informing participants of the requirements of being in the respective study arm, advising participants in the intervention arm if they have met their weekly bus trip target and the subsequent weekly target, coordinating clinic assessments and overall be the main contact point for participants. The unblinded RAs will not be involved in conducting the post randomisation clinic assessments at T2 and T3 or data analysis. The research team member who creates the randomisation sequence will have no contact with participants and will not be involved with data collection or analysis. There are no foreseen circumstances by which unblinding of other research team members would need to occur.

## Data collection, management and statistical methods

12

### Data collection methods

12.1

All participants will complete a baseline assessment (T1), an assessment immediately post-intervention (4 months post intervention commencement, T2) and a follow-up assessment six months post-intervention (10 months post-intervention commencement, T3) to assess if any changes are sustained once incentives are ceased. To maximise participation and ensure acceptable levels of participant burden, a stepped approach will ensure a minimum amount of data collection from all participants, with more burdensome measures related to the secondary outcomes from those willing and able to do so (Table 2). Surveys will be offered electronically, with hard copies provided only if necessary. The survey will include demographic, travel, PA, health and economic related questions. The IPAQ-L is included in the survey because it is reliable, widely used and separates leisure and transport-related PA [35]. The AQoL–8D is a reliable and valid QoL evaluation tool, has Australian population norms, is sensitive to minor changes in QoL and has been included in the survey to complement the health-related questions and to attain health state utility values [36,37]. Permission to use participants' smartcard data is an eligibility requirement and will be sought during the screening and consent process. Data collected from the smartcard includes the date and time (at point of boarding only) of each trip. Smartcard data will be retrieved for the two months prior to commencement of the study (for participants with an existing smartcard) to enable objective assessment of participants’ usual bus use. Participants with a smartphone will be asked to download the state-of-the-art *trips4health* smartphone app. The app uses Global Positioning System (GPS) technology to passively track travel behaviour and automatically infer trips, together with start/end times and travel duration. The app is designed to overcome known limitations of traditional self-report methods (e.g., travel diaries), which are highly burdensome, and among other limitations, poor at picking up short, incidental active transport trips, a critical issue for this study [40]. Participants are prompted each day over a seven-day period to confirm trips are genuine and provide travel mode and purpose through a simple interface with each trip taking a few seconds to code. The app will be introduced at the first clinic assessment, providing a unique face-to-face opportunity to explain how the app works as well as easing known barriers, particularly around privacy.

**Table 2 tbl2:** Stepped levels of assessment participation.

Level of assessment	Survey	Smartcard data	Accelerometer	*trips4health* app	Physical measures
Minimum	✓	✓	✓		
Medium	✓	✓	✓	✓	
	✓	✓	✓		✓
High	✓	✓	✓	✓	✓

Physical measurements (blood pressure, height, weight, waist circumference) will be taken and accelerometers (ActiGraph GT3X and GT3X+) administered at the clinic assessments. All clinic assessments will be conducted at a single clinical research facility. To ensure high quality data collection, respective research team members will be trained according to standardised protocols. Height will be measured using a fixed stadiometer to the nearest 0.1 cm, and weight measured to the nearest 0.1 kg. Waist circumference will be measured at the level of the narrowest point between the lower costal (10th rib) border and the iliac crest using a Figure Finder tape measure. Three blood pressure readings at 1-min intervals will be taken after 5 min of rest (feet flat on the floor, legs uncrossed, back supported, shoulders and arms relaxed, forearms resting on chair/table) using an automated Omron HEM 907 blood pressure device.

Participants will be asked to wear a wrist-worn accelerometer for seven consecutive days, as recommended [41]. Accelerometers accurately and reliably measure step count, PA frequency, intensity and duration and sedentary behaviour [[42], [43], [44]]. Accelerometers will be issued where possible at clinic assessments, but for those unable or unwilling to attend a clinic, accelerometers will be mailed to participants in padded postage packs with instructions provided via telephone. As well as verbal instructions, all participants will receive detailed written instructions for wearing the accelerometer including monitor placement, how to return the monitor via a reply-paid padded postage pack and contact details of the study team, and a brief diary for noting the date of wear and any notable comments (e.g. unwell, forgot to wear). Monitors not returned will be followed up via telephone and email until received.

### Data management

12.2

Participants will complete the survey through REDCap. Physical measurements will be entered into REDCap by a trained research team member. To ensure data quality, range and aberrant data value checks will be set up in REDCap to highlight possible errors. Electronic data collected through the app will be stored in an isolated, single purpose, secure database hosted by Tourism Research Technology (Tasmania, Australia), behind a firewall with limited and restricted organisational access and with appropriate deployment, security and permissions configurations. Once downloaded by the research team, the app data along with all other data will be stored on a secure, password-protected database behind University firewalls. Only members of the research team involved in data analysis will have access to the research data. This study is part of an intended program of work that will take place over several years. For this reason, the data will be kept indefinitely and for no less than 5 years. Participants can give optional consent for indefinite storage of their data. Any data destruction will be via deletion of electronic files. Deidentified data may be used by researchers outside of the investigator team provided that due ethics processes are adhered to.

### Statistical methods

12.3

Quantitative Evaluation: Descriptive statistics (means and proportions) will characterise the outcomes according to group allocation. Participant characteristics will be described and compared across groups. In the unlikely event that there is an uneven distribution of participant characteristics (e.g. gender, age, education) across the control and intervention groups resulting from chance (rather than bias) [45], consideration will be given to clinical meaningfulness and the size of any imbalances that may have occurred [46]. Comparisons will also be made with the general population with the purpose of informing conclusions about the generalisability of the participant groups. Linear mixed model (LMM) regression will compare differences in average daily step count (primary outcome) between control and intervention groups. LMM will also be used to compare differences between the control and intervention groups regarding the secondary outcomes. LMMs allow for missing outcome data and provide methods to account for correlated observations. Analyses will be undertaken on an intention-to-treat basis.

Accelerometer data will be collected using 60-s epochs, and Freedson 1998 equations used to determine cutpoints for sedentary, light, moderate and vigorous intensity physical activities [47]. The impact of applying the criteria of minimum daily wear time (10 h/day), minimum number of days worn (4 days) and minimum number of weekdays and weekend days (3 weekdays and 1 weekend day), as well as consideration of daily wear time values, will be examined in sensitivity analyses [48].

Self-reported domain-specific data from the IPAQ will enable examination of any displacement of leisure-time PA for time spent on public transport and/or in transport-related PA, which could potentially explain null findings.

Secondary analyses to better understand possible enabling factors that may influence adherence to protocols and intervention effectiveness will be undertaken so that appropriate recommendations can be made about future rollout or upscaling of the intervention.

Economic Evaluation: Non-research related resources associated with the implementation of the intervention will be documented and the comparative costs and benefits of the intervention relative to the control group will be assessed. The primary outcome of the economic analysis is a cost comparison between intervention and control groups, that is, a cost-benefit analysis with all costs and benefits expressed in monetary (AUD$) terms.

Modelled analyses will be undertaken to assess the financial implications of broader implementation rollout and intervention upscaling. Personal time (e.g. more/less time spent commuting), productivity and outlay (e.g. walking equipment, fuel, parking) costs will also be evaluated.

Process Evaluation: This will assess the fidelity and quality of implementation, clarify causal mechanisms and identify contextual factors associated with outcome variation [49]. Using the Medical Research Council UK's framework [50] designed for examining complex public health interventions, intervention acceptability at completion of the intervention will be assessed (T2) through face-to-face or telephone interviews with intervention group participants (n = 20 or until saturation of major themes) who did and did not reach bus trip targets. Participants in the intervention arm will be asked if they are willing to participate in an interview when completing the survey at T2. Interviews will be timed to coincide with clinic attendance. The recruitment and implementation impact for the public transport provider will be determined through face-to-face interviews or group discussion with key personnel (n = ≤5) at key points during the implementation of the intervention (i.e. intervention development, mid-intervention and intervention completion). Process evaluation items will be included in all three surveys for all intervention group participants.

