## Outcomes

8

The primary outcome is change in average daily step count measured by accelerometer over seven days at baseline (Timepoint 1/T1), immediately post-intervention (week 17/18; Timepoint 2/T2; primary endpoint) and at the end of the maintenance phase (week 41/42; Timepoint 3/T3). The secondary outcomes are change in: self-reported and measured (via a smartphone app collected over seven days and smartcard data) travel behaviour (e.g. mode (e.g. motor vehicle), frequency and duration); perspectives on travel behaviour (e.g. enablers and barriers); self-reported out of pocket transport-related expenses; self-reported work productivity; self-reported commute time to work/study location; self-reported commute time by different transport modes; self-reported PA (transport, leisure, occupational, domestic, total) (mins/week) and sedentary behaviour (sitting) using the International Physical Activity Questionnaire – Long form (IPAQ – L) supplemented with additional questions in the study-specific survey [35]; accelerometer measured minutes/week of PA, sedentary behaviour and PA intensity; measured blood pressure using a validated automated blood pressure device and waist circumference determined by a measurement tape; body mass index calculated from measured (using a stadiometer and digital scales) or self-reported height and weight; and self-reported health, with quality of life (QoL) measured by the Assessment of Quality of Life (AQoL)-8D [36,37]. Costs incurred by the public transport provider to implement the intervention will be measured by data supplied by the provider at trial completion. All self-reported outcomes will be measured through the study-specific survey at all three timepoints.

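### The accelerometer wear criteria apply only in sensitivity analyses, so the primary daily step count has no wear rule and, read naturally, scores non-wear as inactivity

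*Protocol article*

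**What the plan says.** Section 8 (Outcomes) defines the primary outcome as "change in average daily step count measured by accelerometer over seven days at baseline" and at two later timepoints, with T2 as the primary endpoint: "immediately post-intervention (week 17/18; Timepoint 2/T2; primary endpoint". It sets no minimum wear time and no minimum number of days.

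Section 12.3 (Statistical methods) is the only place where wear criteria appear. They are "minimum daily wear time (10 h/day), minimum number of days worn (4 days", plus 3 weekdays and 1 weekend day. The sentence opens with "The impact of applying the criteria of minimum daily wear time" and closes with "as well as consideration of daily wear time values, will be examined in sensitivity analyses". The primary analysis is described as follows: "Linear mixed model (LMM) regression will compare differences in average daily step count (primary outcome) between control and intervention groups". No wear-time term or non-wear rule is attached to it.

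Section 12.1 gives participants a short diary for wear dates and comments, including having forgotten the device. Nothing links that diary to the primary average. Section 11.2 states that "participants cannot be blinded to treatment allocation".

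**The concern.** A device that is not worn records no steps. Without a wear rule, a forgotten afternoon counts as an inactive one, and the outcome mixes activity with compliance. Two consequences follow.

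- **Attenuation.** Short days lower mean steps in both arms, and shrink a proportional intervention effect with them, even if wear is identical in the two arms.
- **Bias.** Wear at T2 happens after allocation, in participants who know their arm, so randomisation does not guarantee that it is balanced. Any imbalance enters the step contrast directly.

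The mixed model's tolerance of missing outcomes does not help, because a partly worn day arrives as an observed low value and not as a missing one. The article is also not silent on the matter. It names a validity rule and gives it a secondary role, so the issue is a stated choice and not a detail left to another document.

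**Working it through.** **Yardstick.** Section 9 gives a mean of 8000 and SD of 3500 steps/day, a correlation of 0.7, 300 analysed participants, 80% power, alpha 0.05 and a detectable difference of 624. As a share of the mean, 624 / 8000 = 7.8%, which the protocol rounds to 8%. With 150 per arm and alpha taken as two-sided, a difference close to 624 is reproduced only with a variance factor of 1 - 0.7 = 0.3: SD = 3500 × √0.3 = 1917, and (1.96 + 0.84) × 1917 × √(2/150) ≈ 620. The usual baseline-adjusted factor, 1 - 0.7² = 0.51, gives 809. That is a separate matter. Here 624 serves only as the plan's own target effect.

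**What the passages imply.** Examining the impact of applying a rule in sensitivity analyses makes sense only if the main analysis does not apply it. No other section supplies a rule. The natural reading is that all recorded days enter the seven-day average.

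**Attenuation with equal wear.** Assumptions, none from the documents: 10% or 20% of days are short, and on a short day a uniformly distributed 10-66% of the day's steps are captured.
- Mean fraction captured on a short day: (0.10 + 0.66) / 2 = 0.38, so 0.62 is lost.
- 10% short days: 0.10 × 0.62 = 6.2% lost. 20% short days: 0.20 × 0.62 = 12.4% lost.
- A simulation with short days clustered by person agrees: the mean falls from about 8016 to 7516 (6.2%) and from about 8019 to 7020 (12.5%).
- A true proportional effect worth 624 steps would be observed as 624 × 0.938 = 585 or 624 × 0.876 = 547 steps.

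**Bias if wear differs by arm.** Assumption: steps are spread evenly over 14-16 waking hours.
- Steps per hour: 8000 / 16 = 500 to 8000 / 14 = 571.

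| Arm difference in mean wear | Spurious steps/day | Share of 624 |
|---|---|---|
| 0.25 h/day | 125-143 | 20-23% |
| 0.5 h/day | 250-286 | 40-46% |
| 1 h/day | 500-571 | 80-92% |

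- In terms of days: if a short day is 6 of 16 hours, one extra short day per week in one arm shifts the contrast by 8000 × (10/16) / 7 = 714 steps/day. One extra per two weeks shifts it by 357.

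**What a 10 h threshold removes.** Days below 10 h drop out, so a difference caused by short days is essentially removed. A general shift in wear is not. With wear simulated at mean 13 or 14 h, SD 1.5 or 2.5 h, capped at 16 h and one arm shifted by 0.5 h, about 62-95% of the arm difference in wear remains among days of at least 10 h. The threshold therefore needs a wear-time-adjusted analysis beside it.

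**The case against.** The strongest case for the plan as written has four parts.

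- **The averaging rule is inferred.** A reader might conclude that the protocol states that days with an hour or two of wear count as full days. It does not. Day scoring and non-wear detection are not described, and a condensed article may leave them elsewhere. This stands as a limit on certainty. It does not remove the explicit assignment of the criteria to sensitivity analyses.
- **Both analyses will be run, and an all-data primary analysis fits the intention-to-treat statement.** A valid-day rule is itself an exclusion based on behaviour after randomisation. This stands as a cost. However, the sensitivity analyses can only reveal the problem. If they disagree with the primary result, the article gives no basis for preferring them.
- **Differential wear is not shown.** A reader might infer that weekly emails, texts and bus credit in one arm will make wear differ. Those contacts cover weeks 1-16, and T2 wear is in week 17 or 18. The bus credit rewards trips and not device wear. Both arms receive the same assessment credit, wear instructions and monitor follow-up. This stands: carry-over of engagement is possible, but the documents give no evidence of it.
- **Power.** A reader might infer that short days pull the assumed correlation of 0.7 down to about 0.57-0.63. That requires wear errors to be independent between visits. If the same people wear the device poorly each time, the simulated correlation stays at about 0.69-0.75. The 0.7 is also the protocol's assumption for the planned outcome, not for error-free steps. No loss of correlation is claimed here.

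**Conclusion.** The point holds in a limited form. The protocol names a wear rule, confines it and all consideration of wear time to sensitivity analyses, and leaves the primary step count without one. On the natural reading, the headline estimate scores non-wear as inactivity.

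The firmer consequence is attenuation of about 6-12% in mean steps and in any proportional effect, given the assumed 10-20% of short days and 10-66% capture on them. The conditional consequence is a bias of 250-286 steps/day, 40-46% of the target, for each 0.5 h/day by which mean wear differs between arms, given 14-16 waking hours and evenly spread steps. Whether such a difference will arise cannot be told from the documents. The change is worth making because the threat to the primary endpoint is foreseeable and the remedy uses criteria already in the plan.

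**What to change.** Reverse the roles of the two analyses in section 12.3, and state the rule in section 8.

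- Primary: average daily steps over valid days (at least 10 h of wear), requiring the plan's own minimum of 4 valid days. A timepoint that fails this is treated as missing in the mixed model.
- Sensitivity: the all-days average, and a wear-time-adjusted analysis to address wear differences above 10 h. The weekday and weekend requirement can stay among the sensitivity analyses.
- Report wear time and the number of valid days by arm and timepoint.

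The cost is a change of wording with no new data collection. Some participants lose a T2 or T3 value, and the primary analysis then relies on missing at random for those values. The retained all-days analysis shows how much the result depends on that.
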